# Evaluation of interventions to prevent vasovagal reactions among whole blood donors: rationale and design of a large cluster randomised trial

**DOI:** 10.1186/s13063-023-07473-z

**Published:** 2023-08-10

**Keywords:** Vasovagal reactions, Blood donors, Blood donation, Cluster randomised trial, Cross-over, Stepped-wedge, Factorial design

## Abstract

**Background:**

Vasovagal reactions (VVRs) are the most common acute complications of blood donation. Responsible for substantial morbidity, they also reduce the likelihood of repeated donations and are disruptive and costly for blood services. Although blood establishments worldwide have adopted different strategies to prevent VVRs (including water loading and applied muscle tension [AMT]), robust evidence is limited. The Strategies to Improve Donor Experiences (STRIDES) trial aims to reliably assess the impact of four different interventions to prevent VVRs among blood donors.

**Methods:**

STRIDES is a cluster-randomised cross-over/stepped-wedge factorial trial of four interventions to reduce VVRs involving about 1.4 million whole blood donors enrolled from all 73 blood donation sites (mobile teams and donor centres) of National Health Service Blood and Transplant (NHSBT) in England. Each site (“cluster”) has been randomly allocated to receive one or more interventions during a 36-month period, using principles of cross-over, stepped-wedge and factorial trial design to assign the sequence of interventions. Each of the four interventions is compared to NHSBT’s current practices: (i) 500-ml isotonic drink before donation (*vs* current 500-ml plain water); (ii) 3-min rest on donation chair after donation (*vs* current 2 min); (iii) new modified AMT (*vs* current practice of AMT); and (iv) psychosocial intervention using preparatory materials (*vs* current practice of nothing). The primary outcome is the number of in-session VVRs with loss of consciousness (i.e. episodes involving loss of consciousness of any duration, with or without additional complications). Secondary outcomes include all in-session VVRs (i.e. with and without loss of consciousness), all delayed VVRs (i.e. those occurring after leaving the venue) and any in-session non-VVR adverse events or reactions.

**Discussion:**

The STRIDES trial should yield novel information about interventions, singly and in combination, for the prevention of VVRs, with the aim of generating policy-shaping evidence to help inform blood services to improve donor health, donor experience, and service efficiency.

**Trial registration:**

ISRCTN: 10412338. Registration date: October 24, 2019.

**Supplementary Information:**

The online version contains supplementary material available at 10.1186/s13063-023-07473-z.

## Introduction

### Background and rationale

Vasovagal reactions (VVRs), the most common acute complication related to blood donation, are responsible for substantial morbidity, especially when accompanied by complications such as fall and fractures [1–3]. VVRs also discourage individuals to donate again, reducing the likelihood of repeated donations by more than 50% [4, 5]. Furthermore, VVRs can disrupt the throughput and yield of donor sessions due to social contagion “ripple effects” on other donors attending the same sessions [6]. VVRs are not only harmful for donors but also costly and highly disruptive for blood services.

Operating at different stages of blood donation, the principal mechanisms believed to underlie donation-related VVRs include the direct effects of removal of ~500mL of blood; the stress of giving blood (e.g. fear of needles, pain, sight of blood); and orthostatic effects superimposed on a relative hypovolaemic state after donation [7, 8]. Based on this understanding, various strategies to prevent VVRs have been proposed. For example, the World Health Organisation (WHO) recommends pre-donation hydration and applied muscle tension (AMT), a technique to increase blood flow and blood pressure by tensing and releasing muscles. The EU Domaine Project, which also endorses the use of pre-donation hydration and AMT, additionally recommends caffeine loading, distraction techniques, supportive care, and educational material [9–11]. Blood services worldwide have adopted varying strategies to prevent VVRs; water loading and AMT are the most common [12–15].

A previous meta-analysis of randomised trials has, however, shown that there is limited evidence to support water loading or AMT [16–18], because previous studies have typically involved small sample sizes; non-representative populations; non-robust outcomes definitions; and sub-optimal randomisation methods. These concerns apply even more sharply to the sparser evidence available on other interventions used by some blood services, including isotonic drinks [19–21] prolongation of post-donation recovery time, and psychosocial educational materials [22, 23]. Hence, blood services need more robust evidence to help shape and inform their currently diverse approaches to prevent VVRs.

To evaluate the effects of four interventions for the prevention of VVRs among whole blood donors, we have designed the Strategies to Improve Donor Experiences (STRIDES) trial, a large cluster-randomised trial across all sites of the national blood service in England (National Health Service Blood and Transplant [NHSBT]). The trial aims to provide evidence-based policies to reduce VVRs among blood donors, leading to improvements in donor health, donor experience, and service efficiency. A subsidiary aim is to advance understanding of the determinants of VVRs and to develop prevention strategies for VVRs tailored to specific donor sub-populations.

We confirm that recruitment into the trial was ongoing at the time this manuscript was submitted for publication.

### Objectives {7}

The primary objective of STRIDES is to determine the optimum intervention(s) or combination of interventions to prevent VVRs in whole blood donors. A secondary objective is to advance understanding of the determinants of VVRs and to help develop prevention strategies for VVRs tailored to specific donor sub-populations (e.g. stratified by demographic, biological, psychosocial and other characteristics).

#### Hypothesis

We will test the hypothesis that the implementation of one or more interventions, singly or in combination, will reduce VVRs when compared to current practice in NHSBT.

### Trial design {8}

#### Feasibility study

Prior to the initiation of STRIDES, a feasibility study was conducted in five blood donation sites (comprising 3 donor centres and 2 mobile teams) over a period of 15 weeks (25 March 2019 to 26 June 2019) to establish if the protocol for a cluster-randomised trial could be implemented successfully without disrupting routine blood collections. The feasibility study was also used to assess the acceptability of the interventions by blood donors. It showed that the implementation of the four different interventions under evaluation here−either individually or in combination−was practical and did not adversely affect routine blood collection (Supplementary Fig. 1). Furthermore, feedback from donors and staff showed very good acceptability and adherence to the interventions (Supplementary Fig. 2).

#### Main trial design

STRIDES is a cluster-randomised cross-over/stepped-wedge factorial trial of four interventions to reduce VVRs involving randomisation of all 73 blood donation sites (mobile teams and donor centres) of NHSBT in England. Four interventions were compared to current practice in NHSBT (i.e. *vs* standard of care as reference): (i) 500-ml isotonic drink before donation (*vs* current 500-ml plain water); (ii) 3-min rest on donation chair after donation (*vs* current 2 min); (iii) new modified AMT (*vs* current practice of AMT); and (iv) psychosocial intervention using preparatory materials (*vs* current practice of nothing). Each blood donation site (i.e. “cluster”) has been randomly allocated to receive one or more interventions during four 9-month periods (i.e. a 36-month total period) using principles of cross-over (for isotonic drink and time spent in donation chair, to reduce between-cluster confounding and maximise statistical power), stepped-wedge (for the modified AMT and psychosocial interventions, since these interventions cannot be “un-learned” by participants once introduced to the trial) and factorial trial design to construct the temporal sequence of interventions (Supplementary Table 1). A cluster randomised trial design was preferred as it was most practicable for service-wide adoption without disrupting routine blood donation and minimised contamination across interventions.

## Methods: participants, interventions and outcomes

### Study setting {9}

NHSBT collects whole blood from donors at both static donation centres and mobile teams. Recruitment in STRIDES has been taking place in all 73 blood donation sites of NHSBT located across England (Fig. 1). The STRIDES trial has been embedded into the existing routine operational framework of NHSBT (Supplementary Fig. 3). To support additional functions required in the trial, we have established an academic trial coordinating centre at the Department of Public Health and Primary Care, University of Cambridge. In addition to supporting the trial’s core scientific activities, the coordinating centre provides a helpdesk to respond to queries from participants about the trial and maintains a study website (www.strides-study.org.uk). The academic coordinating centre has worked closely with the STRIDES administration team based within NHSBT.

**Fig. 1 Fig1:**
[figure not shown]
A map showing the locations of the blood donation sites. Mobile team points relate to the centre where the team is based, however, teams travel to different locations within their area for whole blood collections

### Eligibility criteria {10}

All blood donors who were eligible to donate and attended a donation site during the study period (2^nd^ of November 2019 to 3^rd^ of November 2022) were included in the trial. Eligibility criteria for donation require that donors are generally fit and well, aged over 17 and weigh between 50 and 158 kg. Donors had the opportunity to opt out of their pseudonymised data being used in the analysis. No donors were excluded from the study unless they chose to opt out.

### Who will take informed consent? {26a}

We have followed the guidance of the Ottawa Statement on the Ethical Design and Conduct of Cluster Randomized Trial [24]. Given the nature of the trial and the interventions used, the need for individual consent was waived by the ethics committee. To alert donors that the study was taking place, poster advertisements have been placed in each trial site. Furthermore, electronic messages about the trial have been sent to all donors prior to its start, plus annual reminders. By completing a simple form, donors have had the opportunity to opt out of the trial, declining the sharing by NHSBT of their pseudonymised data with the academic coordinating centre at the University of Cambridge.

To avoid biases that could undermine the interpretation of study results (e.g. greater awareness of fainting that could result in “social contagion” or other group triggers that lead to increasing fainting), we have not individually informed blood donors about the trial’s specific aim to investigate strategies to reduce VVRs [6, 25]. Instead, if donors asked about changes in donation sessions, donation staff have advised that the changes are being tested for the purposes of enhancing the donation experience (rather than explicitly focusing on VVRs). This communications approach has been consistent with that used in other service-wide changes recently made to routine blood donation practice by NHSBT.

### Additional consent provisions for collection and use of participant data and biological specimens {26b}

As noted above, the need for individual consent into the trial has been waived by the ethics committee. For the STRIDES BioResource sub-study, however, donors have needed to provide their individual and informed consent if they agree to join the NIHR BioResource and provide their surplus blood (taken from the satellite pouch of their routine donation) for research purposes. In particular, donors who have agreed to participate in the STRIDES BioResource have received NHSBT’s routine screening for donation eligibility, i.e. measurement of haemoglobin via copper sulphate test, followed by the Hemocue™ test for those that fail the initial test. Research nurses from NHSBT have, after providing an explanation of the STRIDES BioResource, sought consent from those donors invited to join the STRIDES BioResource. Donors wishing to participate have been asked to complete, with the assistance of a donor carer (if required), an electronic consent form using a tablet device. Alternatively, donors have been able to complete a paper version of the consent form, attached to the back of the Participant Information Sheet.

## Interventions

### Explanation for the choice of comparators {6b}

Interventions are tested versus current NHSBT practice (i.e. the standard of care).

### Intervention description {11a}

As noted above, our trial is evaluating different interventions: (1) 500ml of isotonic drink before donation; (2) 3-min rest on donation chair after donation; (3) modified applied muscle tension (AMT); and (4) a psychosocial intervention using preparatory materials. Table 1 summarises the interventions and key differences from current NHSBT practice. Working across three regional groups, a combination of NHSBT and University of Cambridge staff (including members of the public) have trained NHSBT donor centre staff in trial procedures. All sites began the first set of interventions on the 2^nd^ of November 2019, with changes to interventions occurring every 9 months, according to the pre-specified intervention assignments of the trial’s clusters. As the assessment of intervention effects relies on comparing event rates in periods with and without interventions applied, the 9-month period length was chosen to be long enough to accrue sufficient numbers of the primary outcome events and give contrasts that meet the statistical power requirements.

**Table 1 Tab1:** Details of the proposed interventions

**Type of intervention**	**Mechanism and rationale**	**Content**	**Timing**	**Delivery**	**Key differences with current practice**
**Isotonic drink**	Suggested to prevent both immediate and late-onset VVRs due to its additional effect of decreasing relative hypovolemia and increasing orthostatic tolerance through electrolyte replacement	Isotonic drink (500 ml): ~350 mg sodium, ~0.03g sugar	Before donation	Cup given to all donors with information posters advertised (isotonic drinks prepared prior to donor arrival/tablet given to donor to add to water)	Sodium content to help restore electrolytes lost during donation
**Applied muscle tension**	Physical manoeuvres including tensing/releasing of skeletal muscles to combat orthostatic intolerance Static contractions of the skeletal muscles result in the emptying of large capacitance veins and increased venous return, blood pressure, and ultimately greater cerebral perfusion Other suggested mechanisms include anxiety reduction and distraction	Keeping legs crossed throughout exercise Tensing legs and buttocks and including the abdomen Instructions to “breathe normally” 5-s contractions and release To exercise AMT following donation chair and leaving site, if symptoms	Immediately upon arrival at donation chair	Information handout with instructions given to all donors	Keeping legs crossed throughout exercise (current practice: crossing and uncrossing) Tensing legs and buttocks and including the abdomen (current practice: no abdomen) Instructions to breathe normally (current practice: no breathing instructions) 5-s contractions and release (current practice: 10-s release) To exercise AMT following donation chair or leaving site, if symptoms (current practice; no such recommendation)
**Psychosocial**	Fear, pain, blood-related stimuli, lack of social support, and lack of a sense of control are associated with autonomic regulation, hemodynamic changes, blood pressure changes, and VVRs Preparation materials have been suggested to reduce VVRs	Providing information on the donation process, coping strategies, and various areas of possible apprehension (e.g. fear, pain, physical reactions)	Upon arrival and registration	Information handout given to all donors immediately following registration	Providing relevant information and coping strategies to blood donors directly, including related strategies such as distraction (not currently provided in usual practice)
**Chair**	Following the donation, the hypovolemic state combined with the orthostatic stress of suddenly standing leads to an increased risk of VVRs Recovery time in the donation chair in the upright position after removal of the donation needle has been suggested to attenuate orthostatic stress, reducing the amount of sudden blood pooling and consequent VVRs	Two minutes in donate/recovery position followed by 1 min in the final rest position	Immediately following needle-withdrawal	Chair inclined by staff manually	Duration of time in chair following donation (i.e. a total of 3 min vs. 2 min in current practice)

### Criteria for discontinuing or modifying allocated interventions {11b}

As this pragmatic trial was embedded into routine donation services, the study has been open to the following minor amendments. First, if a participant has not wished to receive the trial’s interventions, they have been able to receive NHSBT’s standard interventions (e.g. water loading rather than the isotonic drink evaluated in the trial). Second, the trial has been conducted during the COVID-19 pandemic, meaning that during the study NHSBT has routinely implemented service-wide revisions with the aim of enhancing donor and staff safety at donation sessions, including limiting the number of donors per session and removing hot drinks previously offered after donations.

### Strategies to improve adherence to interventions {11c}

Using a commercially available feedback device (https://www.feedbacknow.com/), we assessed participants’ adherence to the trial interventions during the feasibility study. Overall, adherence to the new interventions was very similar to that observed with standard NHSBT practice. During the 3-year trial period, we have assessed adherence to interventions by random site visits. Research nurses at NHSBT have visited each blood collection team at least once during each intervention arm, using a protocol to check and record that trial protocols have been followed. Protocol deviations were recorded by the coordinating centre and additional training was carried out if necessary.

### Relevant concomitant care permitted or prohibited during the trial {11d}

During the trial, NHSBT standard care has been in place to ensure donor safety. This includes a screening procedure to ensure the donor is healthy and any medication does not impact donor health or the donation process (including study interventions). As noted above, if a donor has declined to receive the trial intervention, they have been offered standard care.

### Provisions for post-trial care {30}

Given its interventions, this trial is considered minimal risk; no specific post-trial care has, therefore, been provided.

### Outcomes {12}

#### Primary outcome

The primary outcome is the number of in-session VVRs with loss of consciousness (i.e. episodes involving loss of consciousness of any duration, with or without additional complications).

#### Secondary outcomes

Secondary outcomes are (i) all in-session VVRs (i.e. with and without loss of consciousness); (ii) all delayed VVRs (i.e. VVRs with and without loss of consciousness after leaving the donation venue); (iii) delayed VVRs with loss of consciousness; and (iv) any in-session non-VVR adverse events or reactions, such as bruising and rebleeds.

All outcomes will be assessed at the end of the trial and will involve comparison of event rates in periods with and without interventions applied (Appendix 1). The data on the primary and secondary outcomes will be complete by design, as the recording of on-session adverse events, including VVRs, is mandatory in the blood service.

### Participant timeline {13}

All donors who have attended a blood donation session from 4^th^ November 2019 to the 3^rd^ November 2022 have participated in the study, unless they opted out. A baseline visit has been defined as the first time a donor donated during the trial period.

### Sample size {14}

The trial sample size has been informed by (i) the need to generate evidence sufficiently compelling to influence regulators and policy-makers; (ii) NHSBT's duty of care to 900,000 blood donors per year, making it vital for the service to evaluate even small changes in VVR rates; (iii) NHSBT’s objective to optimise blood collection procedures, improve donor return rates, and improve donor (and staff) well-being and satisfaction; and (iv) the need for appropriate power to study determinants of VVRs, both singly and in combination.

Power calculations have been based on the primary endpoint (defined above), assuming a 5% type I error probability and service-wide cluster randomisation (involving 73 teams with ~15,000 whole blood donations per 9-month period per team, and overall primary outcome rate of 0.18% per donation). For the two interventions being assessed using a cross-over design (i.e. isotonic drink and time on donation chair after donation), there is >90% power to detect an odds reduction of >8% (odds ratio of 0.92). For the two interventions being assessed using a stepped-wedge design (i.e. modified AMT and psychosocial intervention), there is >90% power to detect an odds reduction of >13% (odds ratio of 0.87) (Fig. 2). Hence, the study is powered to detect smaller odds reductions than previously reported in the literature but still of importance to blood services. For example, a 10% risk reduction would prevent ~300 severe VVRs per year in NHSBT. All interventions have been tested versus current practice with a 5% overall family-wise error rate control.

**Fig. 2 Fig2:**
[figure not shown]
Statistical power of the trial. Calculated for the two interventions in the study were assessed using a cross-over design (i.e. isotonic hydration and time on donation chair after donation; red line) and the two interventions in the study were assessed using a stepped-wedge design (i.e. modified AMT (applied muscle tension) and psychosocial intervention; blue line). Each intervention was tested at a Bonferroni corrected level (type I error) of 0.0125. The study design has four possible sequences for interventions assessed using a stepped-wedge design (X-I-I-I, X-X-I-I, X-X-X-I, X-X-X-X), and two possible sequences for interventions assessed using a cross-over design (X-I-X-I, I-X-I-X) with a study duration of 3 years and each period lasting 9 months (X = current practice, I = intervention). Power calculations assume 15,000 whole blood donations per 9-month period in each donation centre, with an overall rate of severe (syncope) VVRs of 0.18% per donation and a between-centre variance in log odds of 0.06 (estimated from 2014/15 NHSBT data)

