## Statistical methods

### Statistical methods for primary and secondary outcomes {20a}

#### Principles

Intention-to-treat analyses will be used. Principal analyses will concern the assessment of the main effects of interventions based on outcomes aggregated at the site level (i.e. unit of randomisation). Tests of interaction will assess whether results differ between pre-specified subgroups. Subsidiary analyses will be done using individual-level data with allowance for clustering of observations by site. Multiple testing will be taken into account when interpreting results other than the principal analyses. The trial will be reported according to CONSORT guidelines.

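### Single-step Bonferroni at 0.0125 for the four primary comparisons is valid, but Holm's procedure gives the same 5% family-wise control and never rejects less

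*Protocol article*

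**What the plan says.** The main trial design compares four interventions with current practice ("Four interventions were compared to current practice in NHSBT"). Three places in the protocol article bear on the significance level for these comparisons.

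- **Sample size {14}** bases power on a primary-outcome calculation "assuming a 5% type I error probability", without saying whether that is per test or family-wise. It ends: "All interventions have been tested versus current practice with a 5% overall family-wise error rate control". It names no procedure.
- **The Fig. 2 caption** names one: "Each intervention was tested at a Bonferroni corrected level (type I error) of 0.0125".
- **Principles, under Statistical methods {20a}**, defines the family: "Principal analyses will concern the assessment of the main effects of interventions". It then says: "Multiple testing will be taken into account when interpreting results other than the principal analyses".

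End-of-trial analyses, which specifies the primary model, gives no level and no multiplicity procedure. Whether tests are one- or two-sided is not stated anywhere. No step-down procedure is mentioned.

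**The concern.** The family is four main effects, and the promised guarantee is 5% family-wise error. Single-step Bonferroni meets that guarantee but holds every test at 0.0125, even after other hypotheses in the family have been rejected. Holm meets the same guarantee and relaxes the threshold as rejections accumulate. For example, if three interventions have already been declared effective, p = 0.03 for the fourth is a rejection under Holm (threshold 0.05) and not under Bonferroni.

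This bears on the trial's own aims. The primary objective is to find the best intervention or combination, so more than one true effect is a scenario the factorial design is built for, and the sample-size section stresses the value of detecting small changes in reaction rates.

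A smaller, related point is wording. Taken alone, the sentence under Principles could suggest that multiplicity is considered only outside the main effects, and the methods section is where an analyst would look for the rule.

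**Working it through.** **The stated level.** 0.05/4 = 0.0125, exactly as in Fig. 2. For four independent tests the family-wise error is 1 - (1 - 0.0125)^4 = 0.049.

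**Why Holm keeps the guarantee.** Order the four p-values and compare them in turn with 0.05/4 = 0.0125, 0.05/3 = 0.0167, 0.05/2 = 0.025 and 0.05, stopping at the first failure. With m true null hypotheses, a first false rejection requires one of those m p-values to be at or below 0.05/m. The probability of that is at most m × 0.05/m = 0.05, whatever the dependence. Any p-value at or below 0.0125 passes every step it meets, so Holm rejects all that Bonferroni rejects.

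**Inputs for power** (Sample size {14} and Fig. 2): "73 teams with ~15,000 whole blood donations per 9-month period per team"; four periods; event rate 0.18%; between-centre variance 0.06 on the log-odds scale; the listed sequences; odds ratios 0.92 (cross-over) and 0.87 (stepped-wedge). Assumed: sites split equally over sequences, equal site sizes, no site-by-period variance, 0.18% as the control rate.

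*Cross-over.* Donations: 73 × 15,000 × 4 = 4,380,000, so 2,190,000 per condition. Expected events: 2,190,000 × 0.0018 = 3,942 on control and about 3,627 at odds ratio 0.92. SE of the log odds ratio ≈ √(1/3,935 + 1/3,621) = 0.0230, using N·p·(1 - p) in each condition. Expected z = |ln 0.92|/0.0230 = 3.62.

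*Stepped-wedge.* A mixed-model information calculation with a site random effect and four period effects gives SE 0.0389. Expected z = |ln 0.87|/0.0389 = 3.58.

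**Power at the stated odds ratios:**

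| Level | OR 0.92, cross-over | OR 0.87, stepped-wedge |
|---|---|---|
| two-sided 0.0125 | 86.9% | 86.1% |
| one-sided 0.0125 | 91.6% | 91.0% |
| two-sided 0.05 | 95.2% | 94.8% |

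The plan's figure of more than 90% is therefore reproduced at one-sided 0.0125. At two-sided 0.0125 power is 86-87%, or about 88% if 0.18% is read as the overall rather than the control rate.

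**Bonferroni against Holm.** 1,000,000 simulated sets of four independent two-sided z-tests, with expected z of 3.62 or 3.58 for effective interventions and 0 otherwise:

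| Effective interventions | Power per effective intervention, Bonferroni | Same, Holm | Family-wise error, Bonferroni | Same, Holm |
|---|---|---|---|---|
| none | – | – | 0.049 | 0.049 |
| one | 87% | 87% | 0.037 | 0.047 |
| two | 87% | 89% | 0.025 | 0.046 |
| three | 86-87% | 91% | 0.012 | 0.044 |
| all four | 86-87% | 94% | – | – |

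The chance of showing all four, when all four work, is 56% under Bonferroni (check: 0.869² × 0.861² = 0.56) and 81% under Holm. With the slightly smaller SEs that follow from reading 0.18% as the overall rate (about 0.0226 and 0.038), the all-four case goes from about 88% to 95% per intervention and from 60% to 83% jointly. The pattern does not depend on that choice.

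**The case against.** The strongest reply is that nothing here is wrong. Bonferroni at 0.0125 delivers exactly the control promised under Sample size {14}, and the choice between two valid procedures might be left to an analysis plan that is not shown. The 0.0125 appears only in a power-figure caption, so it may be no more than a planning level. That stands as far as it goes: this is an improvement in efficiency, not the correction of an error. But the caption speaks of how each intervention was tested, and the alternative has the same guarantee at almost no cost.

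It is also fair that the large gains need several true effects. The article's hypothesis is only that one or more interventions work, and with one the gain is nil. Bonferroni also has simultaneous intervals that match its decisions, which suits a trial meant to inform policy. Both points stand.

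Two stronger readings are tempting.

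- A reader might infer from the sentence under Principles that the four main effects are tested at 5% each, giving a family-wise error of up to 1 - 0.95^4 = 18.5% with independent tests. The documents do not support this. Sample size {14} and Fig. 2 both state correction for these comparisons, and the sentence can be read alongside them as covering everything else. It is an ambiguity of wording.
- A reader might infer that the claimed power of more than 90% is wrong. The article does not state sidedness, and one-sided 0.0125 reproduces the claim, so the lower figures here depend on the two-sided assumption.

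**Conclusion.** The point holds as a cheap improvement. The plan's control of family-wise error is valid; Holm gives the same control under any dependence and cannot reject less. Power per intervention rises by essentially nothing if one intervention works, by about 2 points if two work, and by about 7-8 points if all four work at the design odds ratios.

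The sizes assume two-sided tests, independent test statistics, equal allocation to sequences and no site-by-period variance. The allocation table that would show any correlation between the intervention estimates is in a supplement that is not shown. Correlation would change the size of the gain but not the validity of Holm.

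**What to change.** - **Principles and End-of-trial analyses:** state that the four primary-outcome main effects are tested by Holm's procedure at a 5% family-wise level (smallest p-value against 0.0125, then 0.0167, 0.025 and 0.05), and state the sidedness.
- **Multiplicity sentence under Principles:** say that the main effects fall under the family-wise control in Sample size {14}, and that multiplicity is weighed in interpretation for all other results.
- **Fig. 2:** keep 0.0125 as the conservative planning level. The curves were calculated at it, and power under Holm depends on how many other interventions work.
- **Reporting:** make Holm-adjusted p-values the decision rule. Give either 98.75% Bonferroni intervals or 95% intervals labelled as unadjusted, and say that intervals and decisions can differ. A 98.75% interval may include 1 where Holm rejects, and an unadjusted 95% interval may exclude 1 where Holm does not.
- **Timing:** fix this before outcomes are analysed by arm. The article says analysts are not blinded, so relaxing a published threshold after by-arm results are known would be open to a post-hoc objection; in that case 0.0125 should stand.

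The cost is a few sentences and less simple simultaneous intervals. The sample size and data collection do not change.
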